## 1.2 Rationale

Children with serious pediatric illnesses who live in households with food –related insecurities are at risk for disparities in health and QOL outcomes by three pathways. One pathway of risk is illness-related financial burden, which leads to compensatory cost coping. North Carolina (NC) has shamefully high rates of adolescent poverty; 19.5% of children in NC live in household poverty, and 45% reside in high poverty neighborhoods.[26] Not only do these statistics apply to

[figure not shown]

**Figure 2: Conceptual model of food and nutrition insecurity in serious pediatric illness** (adapted from [name], & Kneipp, 2018; and Berkowitz, et al., 2023)

children newly diagnosed with cancer but an additional 15% of affected households are expected to fall into poverty during the first 6 months following the child's diagnosis.[27] Parental work disruptions are highly prevalent (77%) and, in 30-50% of households, one parent ceases paid

work to manage the child's caregiving requirements.[27] Increases in payer-patient cost-sharing (deductibles, co-insurances, co-pays) and out-of-pocket expenditures for healthcare-related travel and lodging near the treatment center contribute to the financial burden.[28] Households with limited English proficiency, low incomes, residences  $\geq 60$  miles/minutes from the treatment center, caregiving-related work disruptions and/or headed by single women are at high risk for catastrophic ( $>40\%$  of annual household income[29]) illness-related financial burden.[30] This financial burden generates compensatory cost coping whereby parents divert resources ordinarily used to meet basic needs (nutritious food) toward paying medical bills and illness-related out-of-pocket expenses, particularly as funds shrink towards the end of the month and financial burdens do not.[31-33] Among US households reporting food insecurity, 68.4% had incomes in the prior tax year that disqualified them for government food assistance.[34] For qualifying households of patients diagnosed with cancer, their allotted assistance is not adjusted to account for the additional expenses generated by cancer.[35]

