#### **3.3 Exploratory**

- 3.3.1 *Signals of improvement in food insecurity, nutrition insecurity, cost-coping behaviors, time demands, and financial well-being is defined by improvements in T4 (post intervention) measurements as compared to T1(baseline pre-intervention).*
- 3.3.2. *Adolescent and parent thoughts about MTM-Kids processes, the meals, and recommended improvements in the meals and study processes are defined as themes that emerge from analyses of qualitative interviews with the adolescents, and with their parents.*
-

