### Footnotes to Time & Events Table

1. Screening includes tests to confirm eligibility.
2. Informed consent will include (a) adult consent from the parent for their participation in the study, (b) parental permission for their adolescent's participation, and (c) adolescent assent. HIPAA authorization to extract a

limited set of data from the adolescent's electronic medical record. Completion of the parent contact form, baseline assessments and Equiti Food account set-up will commence after the written consent/permission/assent have been obtained.

3. Parent participants must register with the Equiti Foods Website in order to select and order MTM allotment. Allotment will be weekly (up to 10 meals per week), for 12 weeks. Delivery will take 3-5 days and parents can order up to 5 working days in advance.
  4. Adolescents will complete surveys at baseline, T2, T3 and T4. See [ADOLESCENT SURVEYS](#)
  5. Parents will complete surveys at baseline and at 12 weeks (T4). See [PARENTAL SURVEYS](#)
  6. A limited set of data (specified in the HIPAA authorization form) about the adolescent's cancer diagnosis, diagnosis date, treatment protocol, treatment initiation date, and treatment exposures to date will be extracted from the adolescent's electronic medical record.
  7. Gift cards will be given following completion of the Baseline and then the 12-week survey, and following completion of the Week 4, 8 and 12 interviews. The gift cards value will be \$15 for parent and \$15 for the child, for a possible total of \$75 for parent and \$75 for child.
  8. Parents will be contacted within 1 week following baseline data collection to verify that they have placed the initial meal order, and problem-solve as indicated.
  9. Semi-structured interviews will be conducted and audio-recorded via an IRB-approved secure video platform, or in-person during a regularly scheduled clinical visit according to the participant's preference. An investigator-developed interview guide will inform the interviews (see [APPENDIX III – Study Semi-Structured Interview Guides](#)).
-

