### **5.1 Inclusion Criteria**

1. Written informed parental permission plus adolescent assent to participate in the study plus HIPAA authorization for release of personal health information.
2. Adolescent is willing and able to comply with study procedures based on the judgement of the investigator.
3. Adolescent is age 12-17 years and can use English for complex communication
4. Adolescent has completed at least one cycle of cancer chemotherapy and expects to undergo at least 2 more cycles.
5. Eligible parents of adolescent subjects:
  - Aged 18 years or older
  - Primary caregiver of a study-eligible adolescent
  - Screens positive for household material hardship (food, nutrition, utility, or transportation insecurity)
  - Uses English or Spanish for complex communications

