### **7.2.2 Surveys and Interview Questions for Parents**

Parents will be asked to complete established measures of household food and nutrition insecurity, time-demands, financial cost-coping behavior and financial wellbeing,

Household food insecurity will be measured by the 6-item Food Security Scale [53]. Parents will be asked to indicate whether they experienced the condition during the past 3 month and, in some cases, how often. Scores will be estimated by counting the number of affirmative responses (yes, sometimes, or often); these scores can be categorized, such that 0-1=very low food insecurity, 2-4= low food insecurity, and 5-6=high food insecurity. [53]

Household nutrition insecurity will be measured by the 4-item Nutrition Security Scale plus 2 items from the Healthfulness Choice Scale. [54] Parents will be asked to use a 5-point scale, anchored by 1=never and 5=always, plus a don't know/prefer not to answer option. Scores will be estimated by counting the number of affirmative responses (sometimes, often, or always); these scores can be categorized such that 0-

---

1=very low nutrition insecurity, 2-4= low nutrition insecurity, and 5-6=high nutrition insecurity. [54]

Parental role time-demands will be measured with a set of Patient-Reported Outcome Measurement System v.2 (PROMIS v.2) items that ask about satisfaction with perceived social role performance. [55] Parents will be asked to respond to the PROMIS items using a 5-point scale anchored by 1=not at all and 5=very much. Item responses will be summed and scored using the T-score metric. Higher scores indicate greater satisfaction with social role performance. [55]

Financial coping behaviors will be measured by 7 of the questions from the Financial Coping Behaviors Scale currently being asked in a study of financial distress during treatment of pediatric acute lymphoblastic leukemia (ALL; ACCL20N1CD). [56] Parents participating in MTM-Kids will only be asked about financial coping strategies with implications for the health of the adolescent or another family member. Parents will be asked to use a 3-point response scale anchored by 0=never and 2=several times) to indicate how often they used each coping behavior in the prior month. Item responses will be summed for a total score that can range from 0-14.[56]

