## 15.2.2 PARENTAL SURVEYS

### 15.2.2.1 Food Insecurity

These statements are what people have said about their food situations. Please tell us whether the statement was often true, sometimes true, or never true for you in the last 6 months.

1. "The food that I bought just didn't last, and I didn't have money to get more."
    - a. Often true
    - b. Sometimes true
    - c. Never true
    - d. Don't know or prefer not to answer
  2. "We couldn't afford to eat balanced meals."
    - a. Often true
    - b. Sometimes true
    - c. Never true
-

- d. Don't know or prefer not to answer
- 3. In the last 3 months, did you or other adults in your household ever cut the size of your meals or skip meals because there wasn't enough money for food?
  - a. Yes
  - b. No (Skip AD1a)
  - c. Don't know or prefer not to answer (Skip AD1a)

[If YES above, then]

- 4. How often did this happen – almost every month, some months, but not every month, or in only 1 or 2 months?
  - a. Almost every month
  - b. Some months but not every month
  - c. Only 1 or 2 months
  - d. Don't know or prefer not to answer
- 5. In the last 3 months, did you ever eat less than you felt you should because there wasn't enough money for food?
  - a. Yes
  - b. No
  - c. Don't know or prefer not to answer
- 6. In the last 3 months, were you ever hungry but didn't eat because there wasn't enough money for food?
  - a. Yes
  - b. No
  - c. Don't know or prefer not to answer

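### For parents enrolled soon after diagnosis, the 3-month recall at T1 mostly describes life before the illness, which dilutes the exploratory T4-versus-T1 signal

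*Protocol*

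**What the plan says.** Four rules in the protocol combine here.

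- **Entry (5.1).** "Adolescent has completed at least one cycle of cancer chemotherapy and expects to undergo at least 2 more cycles". There is no minimum or maximum time since diagnosis.
- **Recall.** Section 7.2.2 describes the food scale thus: "Parents will be asked to indicate whether they experienced the condition during the past 3 month and, in some cases, how often". In appendix 15.2.2.1, items 3, 5 and 6 follow this, for example "In the last 3 months, did you ever eat less than you felt you should because", and all six nutrition items in 15.2.2.2 also look back 3 months. The lead-in to food items 1-2 differs: "whether the statement was often true, sometimes true, or never true for you in the last 6 months".
- **Signal (3.3.1).** It is defined as "improvements in T4 (post intervention) measurements as compared to T1(baseline pre-intervention"). Section 8.3.3 describes T1 and T4 for the sample as a whole. Section 8 adds SDs and confidence intervals for the change, and uses upper 80% limits when sizing the future trial.
- **Expected drift (1.2).** The rationale is that diagnosis itself creates hardship: "an additional 15% of affected households are expected to fall into poverty during the first 6 months following the child's diagnosis".

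The date needed to align the windows is available. Footnote 6 to the Time & Events Table lists "diagnosis date, treatment protocol, treatment initiation date, and treatment exposures to date will be extracted", and form 15.2.1.1 has a field for the diagnosis date. Section 8.3.3 uses treatment exposures for the qualitative work but does not use time since diagnosis in the T1-T4 comparison.

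**The concern.** A before-after comparison in one arm relies on the two periods being alike except for the meals. For a parent who enters shortly after the first cycle they are not alike: T1 recall reaches back into ordinary life before the illness, and T4 recall lies wholly within it. If hardship rises with diagnosis, as the protocol argues, the no-effect expectation for that parent is worsening rather than zero change. A parent who enters three months or more after diagnosis compares like with like. The planned summary pools both kinds.

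Two uses are at stake. Section 1.2 names the sensitivity of the proposed pathways to the meals as an uncertainty to settle before a definitive trial, so a diluted signal bears on that decision. The SD of change that feeds the next sample size would also contain a component due only to when dyads happened to enrol.

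**Working it through.** The protocol gives no expected change, rate or power for this comparison, so there is no figure to reproduce.

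**Inputs from the protocol:** 3-month recall, taken as 91 days; T4 at 12 weeks (84 days) after meals start (4.1); 19.5% household poverty among the state's children, and a further 15% of affected households within 6 months of diagnosis (1.2).

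**Assumptions:** days *d* from diagnosis to T1 of 21-42 for a single-cycle entrant; hardship at a constant level before and another constant level after diagnosis.

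**Step 1, T1 window.** Pre-diagnosis share *f* = (91 − *d*)/91. It exceeds one half when *d* is below 45.5 days.

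**Step 2, T4 window.** T4 falls at least 84 days after T1, so a 91-day look-back reaches at most 7 days before T1. With *d* of 21 or more it is wholly post-diagnosis.

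**Step 3, dilution.** Set pre-diagnosis hardship to 1 and post-diagnosis hardship to *k*. Then T1 = *f* + (1 − *f*)*k*, and T4 with a true 50% cut = *k*/2. The poverty proxy is *k* = (19.5 + 15)/19.5 = 1.77.

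- *d* = 21: T1 = 0.769 + 0.231 × 1.77 = 1.178; T4 = 0.885; apparent cut = 1 − 0.885/1.178 = 25%.
- *d* = 42: T1 = 0.538 + 0.462 × 1.77 = 1.355; T4 = 0.885; apparent cut = 35%.

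**Step 4, complete loss.** T4 fails to beat T1 when *k*/2 ≥ *f* + (1 − *f*)*k*, that is *k* ≥ *f*/(*f* − 0.5), possible only if *f* > 0.5.

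| Days to T1 | Pre-diagnosis share of T1 | Apparent cut (true 50%, *k* = 1.77) | *k* at which the signal is lost |
|---|---|---|---|
| 21 | 77% | 25% | 2.9 |
| 28 | 69% | 28% | 3.6 |
| 35 | 62% | 32% | 5.3 |
| 42 | 54% | 35% | 14 |
| 49 | 46% | 37% | never |
| 91 | 0% | 50% | never |

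**Step 5, check on yes/no items.** For a 13-week item that is affirmed if the event ever happened, with T1 at 4 weeks and assumed weekly chances of 3% before and 10% after diagnosis:

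- T1 = 1 − 0.97^9 × 0.90^4 = 0.501.
- T4 without effect = 1 − 0.90^13 = 0.746.
- T4 with the weekly chance halved = 1 − 0.95^13 = 0.487.

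The halving still shows as a gain, but a very small one. With 2% before, T1 is 0.453 and the same halving looks like a 3-point worsening. With 5% before, T1 is 0.586 and the gain is 10 points, against 26 points if T1 lay wholly after diagnosis.

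**Step 6, the 6-month wording.** Under the lead-in to food items 1-2 (182 days), the pre-diagnosis share of the T4 window is (182 − *d* − *g*)/182, where *g* is the T1-T4 gap. With *g* = 91 it is 38% at *d* = 21 and 27% at *d* = 42; with *g* = 84 it is 42% and 31%. About half of the T4 window ((182 − *g*)/182, 50-54%) then repeats the T1 window.

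**The case against.** The case against is substantial, and much of it stands.

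- **Who is affected is unknown.** One cycle is a minimum. Recruitment is from the clinic schedule and social-work referral (4.2), so patients at any stage can enter. Cycle length and time to T1 are not given, and beyond about 45 days T1 is no longer mostly pre-diagnosis.
- **The rates are assumptions.** With weekly chances of 5-15% after and 0-6% before diagnosis and T1 at 3-6 weeks, the cut needed just to show no change runs from about −15% (where the earlier rate is the higher) to 76.5%. A reader might infer that a halving of hardship would be missed outright. The documents do not support that: it needs a rise of roughly threefold or more, and their own proxy gives 1.77. Poverty is also not the same thing as food hardship.
- **The yes/no model fits few items.** It suits food items 3, 5 and 6. Item 4 is a follow-up to item 3, and the nutrition items are graded from never to always, with rarely not counted as affirmative.
- **Direction.** A reader might infer that the pooled change is biased against the meals. Only this mechanism runs that way. Dyads are selected on a hardship screen with a 6-month look-back (15.2.2.8), and regression to the mean can produce apparent improvement. The screen can also pick up households already in hardship before diagnosis, for whom *k* is near 1 and dilution is slight.
- **Stakes.** The endpoint is exploratory and descriptive, and section 8 already warns that effect estimates from feasibility data are unreliable. A split by time since diagnosis could also be left to an analysis plan that is not shown.

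The timing mismatch itself survives, because eligibility, recall period and the definition of improvement are all fixed in this protocol.

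**Conclusion.** The point holds as a limit on how 3.3.1 can be read, not as a flaw in the trial's main result. For dyads surveyed within about 45 days of diagnosis, T1 on the 3-month items is mostly a pre-illness measurement and T4 is not. Under the poverty proxy a true 50% cut appears as about 25-35%; complete loss needs roughly a threefold rise or more. These sizes rest on assumed days to T1, constant hardship before and after diagnosis, and poverty standing in for food hardship. The net direction of the pooled change and the proportion of early entrants cannot be determined from the protocol. Recruitment and retention, the primary endpoint, are untouched.

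The recall periods in 7.2.2 and in the lead-in to food items 1-2 contradict each other. Under the 6-month version the two windows overlap and an early entrant's T4 still reaches before diagnosis.

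**What to change.** 1. In 8.3.3, keep the pooled summary and add each parent's T1-T4 change in food and nutrition insecurity by time from diagnosis to T1: under 3 months versus 3 months or more, or an individual plot against that time. Use the abstracted diagnosis date.
2. State that T1 is partly pre-illness for early entrants, both when interpreting 3.3.1 and when carrying the SD of change into the future sample size.
3. Reconcile the recall period in 7.2.2 with the lead-in to food items 1-2 in 15.2.2.1.

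Confining any claim of improvement to parents at 3 months or more is not recommended: with 15 dyads that group could be very small, and the effect of the hardship screen would remain in it.

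The cost is one descriptive display, a sentence or two of text and one wording correction. No new data, visits or eligibility changes are needed. The downside is small descriptive groups.

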### **5.2 Exclusion Criteria**

1. Adolescent or parent uses language other than English or Spanish to communicate

### **5.3 Single Subject Exceptions**

Eligibility single subject exceptions are not permitted for Lineberger Comprehensive Cancer Center Investigator Initiated Trials under any circumstances. Once a subject is eligible and enrolled, other types of single subject exceptions may be allowed if proper regulatory review has been completed in accordance with Lineberger Comprehensive Cancer Center's Single Subject Exceptions Policy.

### **5.4 Participant Replacement**

Participants who provide informed consent, parental permission, or adolescent assent and subsequently withdraw or are removed prior to meeting the requirements of evaluability for the primary endpoint may be replaced to obtain the stated number of evaluable participants for the study.

---

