### **3 STUDY ENDPOINTS**

#### **3.1 Primary Endpoint**

- 3.1.1 *Feasibility of recruitment and retention of a study sample for a future efficacy trial of MTM-Kids intervention to mitigate food-related insecurities for households of adolescents in active treatment with chemotherapy for pediatric cancer is defined as 70% enrollment, 70% completion of baseline and Week 12 surveys, and 70% receipt of at least 4 weeks of meal deliveries + completion of at least one interview by adolescent and by parent (either week 4, 8 or 12)*

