## **6 STUDY CONDUCT**

### **6.1 Duration of Intervention**

Intervention may continue for 12 weeks or until:

- Either the adolescent or parent decides to withdraw from study treatment.
- General or specific changes in the child's condition render them unacceptable for further participation in the judgment of the investigator.
- Significant study intervention or activity non-compliance.

If the subject is removed from the intervention, the Principal Investigator should be notified. The reason for discontinuation of a protocol intervention will be documented in the medical records and on the eCRF. In the case where an adolescent or parent decides to prematurely discontinue protocol intervention ("refuses intervention"), the adolescent or parent should be asked if they may still be contacted for further scheduled study assessments. The outcome of that discussion should be documented in the medical records and in the eCRF.

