## **8.3      Data Analysis Plans**

### **8.3.1      *Primary Endpoint Analysis***

For project to be considered successful and feasible in a larger study, we determined the following benchmarks: a) 70% of those approached are enrolled in the study, (b) 10 out of 15 participating parent/adolescent dyads should complete the baseline and week 12 surveys, (c) 10 out of 15 parents receive at least 4 weeks of meal deliveries, and (d) in 10 out of 15 dyads, the adolescent and the parent each complete at least one interview (week 4, 8, or 12). We will estimate the retention rate and report it with a 95% confidence interval.

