#### **8.3.4**     *Interim Analysis*

When 5 adolescent-parent dyads (formative test) have completed study requirements, their data will be analyzed as described above, study processes and the MTM-Kids intervention will be refined as needed, and then the validation test will commence.

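### Section 5.4 lets withdrawn or removed participants be replaced although the primary endpoint is retention, and nothing keeps the replaced dyads in the denominator

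*Protocol*

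**What the plan says.** Protocol 3.1 sets the primary endpoint as "70% enrollment, 70% completion of baseline and Week 12 surveys, and 70% receipt of at least 4 weeks of meal deliveries", together with at least one interview by each member of the dyad. Protocol 8.3.1 turns the retention parts into counts: "10 out of 15 participating parent/adolescent dyads should complete the baseline and week 12 surveys"; "10 out of 15 parents receive at least 4 weeks of meal deliveries"; and the interview requirement met in 10 of 15 dyads. It adds: "We will estimate the retention rate and report it with a 95% confidence interval". No denominator is named for that rate. Section 8.2.2 fixes total accrual at 30 people, that is 15 dyads, with no allowance for replacements.

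Protocol 5.4 provides that consented participants who "subsequently withdraw or are removed prior to meeting the requirements of evaluability for the primary endpoint may be replaced to obtain the stated number"; the number meant is the count of those evaluable. The protocol does not define evaluability. Section 6.4 treats a parent who stays unreachable as withdrawn, so loss to follow-up falls under this rule as well. Under 6.5, withdrawal of consent by either member takes the participants off study.

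Section 6.3 says that too many withdrawals can make the study not feasible. Section 8 carries enrollment and retention data into the sample size of the future efficacy trial.

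**The concern.** Replacing dropouts is harmless when the endpoint is something else and dropout is a nuisance. Here dropout is the outcome. A dyad that leaves before the week 12 survey, before four weeks of deliveries or before its interviews has failed the benchmark concerned. If another dyad takes its place and the count is still out of 15, a failure has been removed because it failed.

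Two decisions rest on the result. Section 8.3.1 makes the benchmarks the test of whether a larger study is feasible, and section 8 uses the retention data to size that study. An upward bias makes a go decision more likely and the allowance for dropout in the next trial too small.

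**Working it through.** **The plan's own figure.** The benchmark is 10/15 = 66.7%. From 3.1.1, 0.70 × 15 = 10.5, so 70% of 15 would need 11 dyads. The stated 10 is a slightly looser rule; that is a separate inconsistency, but it matters for the wording of the fix.

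**Inputs.** From the protocol: 15 dyads and a benchmark count of 10. Assumed, because the protocol gives neither: true retention p, and the share f of failures that are replaced. Dyads that stay enrolled but miss surveys, meals or interviews are not replaceable under 5.4, so f is normally below 100%.

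**Model.** Each of the 15 places is filled by one dyad. A failing dyad is replaced with probability f, at most once, by a dyad with the same p, and the replaced dyad is not counted. Then:

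- apparent retention: s = p + (1 − p) × f × p
- chance of meeting the benchmark: P(X ≥ 10), X ~ Binomial(15, s)
- expected dyads consented: 15 × [1 + (1 − p) × f]

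At p = 0.50:

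| f | s | P(≥ 10/15) | dyads consented |
|---|---|---|---|
| 0 | 50% | 15.1% | 15 |
| 25% | 0.5 + 0.5 × 0.25 × 0.5 = 56.25% | 29.4% | 16.9 |
| 50% | 0.5 + 0.5 × 0.50 × 0.5 = 62.5% | 48.3% | 18.8 |
| 100% | 0.5 + 0.5 × 1 × 0.5 = 75% | 85.2% | 22.5 |

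At other values of p, for f = 0, 25%, 50% and 100%, the chance of reaching 10/15 is:

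- p = 0.40: 3.4%, 8.9%, 19.1%, 53.2%
- p = 0.60: 40.3%, 59.7%, 77.8%, 97.7%

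The bias is upward for every f above zero. The f = 100% column is the upper bound under the assumption of one replacement per failure.

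**One concrete outcome.** Five dyads are replaced, and 10 of the final 15 complete. With the replaced dyads dropped, the report shows 10/15 = 66.7% (Clopper-Pearson 95% CI 38.4% to 88.2%), which meets the benchmark. With all consented dyads counted, it is 10/20 = 50.0% (27.2% to 72.8%), against 0.70 × 20 = 14 needed.

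**Effect on the next trial.** Suppose its sample size is inflated by dividing by the retention rate (an assumption; section 8 does not give the formula). Then 66.7% gives a factor of 1/0.667 = 1.5, and 50% gives 1/0.50 = 2. Recruiting 1.5 times the required number at 50% true retention leaves 0.75 of it.

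**The case against.** The strongest reply is that dropping replaced dyads is inferred. Section 5.4 permits replacement; it does not say that the replaced participants' data are discarded. Section 8.3.1 names no denominator for the retention rate, and 6.3 asks for withdrawals and their reasons to be recorded and treats them as evidence on feasibility. This stands: the bias is conditional on how 5.4 is applied. But nothing in the protocol keeps replaced dyads in, and a benchmark and accrual both fixed at 15 dyads point towards leaving them out. Discretion to replace after seeing who has left is no safeguard.

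Second, not every failure can be replaced, and time limits replacement. Loss to follow-up needs three missed visits (6.4). With 9 months of accrual in a 12-month study and 12 weeks per dyad, a late loss could hardly be replaced and followed. This also stands, and it is why the result is a range, with full replacement only as a bound.

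Three stronger readings are tempting but unsupported:

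- A reader might infer that evaluable means having completed the endpoint requirements, so that retention approaches 100% by construction. All 15 dyads would then be completers and a benchmark of 10 of 15 would mean nothing.
- A reader might take "Significant study intervention or activity non-compliance" in 6.1 as automatic endpoint failure. That item ends the intervention. It is not an off-study criterion in 6.5, and 6.1 asks those who choose to stop early whether assessments may continue. A dyad stopped after four weeks of meals and one interview each, which then completes the week 12 survey, meets every retention benchmark.
- A reader might extend the bias to the whole primary endpoint. Benchmark (a), enrollment among those approached, is not inflated by dropping replaced dyads.

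An SAP not shown might define the denominator. The replacement rule is nevertheless in the protocol, where it conflicts with the protocol's own endpoint.

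**Conclusion.** The point holds in conditional form. The replacement rule conflicts with a retention endpoint, and the protocol does not keep replaced dyads in the denominator. If they are left out, retention and its interval are biased upward. The size cannot be fixed from the document. At an assumed 50% true retention with one replacement per replaced failure, the apparent rate lies between 56% and 75%, and the chance of passing between 29% and 85% instead of 15%, as the replaced share runs from 25% to 100%. The document shows a rule that allows this inflation; it does not show that it will occur or how large it will be. Because the rule bears on the primary endpoint and costs little to correct, it should be settled before results are read.

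**What to change.** State in 5.4 and 8.3.1 that every consented dyad stays in the retention denominator and counts as not retained on any benchmark it had not met before withdrawal, removal or loss. Extra dyads may be enrolled to supply interview data, but they add to the denominator. Express the retention benchmarks as at least 70% of all enrolled dyads, as in 3.1.1. Define evaluable, or remove the term, and reconcile the accrual of 30 in 8.2.2 with any extra dyads.

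The cost is protocol wording. The reported retention may look less favourable. At exactly 15 dyads, at least 70% means 11 and not 10, which at a true retention of 70% lowers the chance of meeting a single benchmark from 72% to 52%. The sponsor should accept that knowingly.
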